### Inclusion criteria

•Aged 18–50 years

•Primary diagnosis of autism spectrum disorders (based on criteria by psychiatrists from the text revision of the diagnostic and statistical manual of mental disorders, fourth edition)

•A full intelligence quotient of at least 85 and a verbal intelligence quotient of 100 or above

•Autism Diagnostic Schedule or Autism Diagnostic Interview, Revised score above the autism spectrum disorders cut-off point

•Educational qualifications: high school graduate or beyond

•Informed of his or her diagnosis

•Aware that he or she has poor emotional self-awareness or ability to express emotion and difficulty understanding others’ emotions and thoughts

•Willing to participate in the study

### Exclusion criteria

•A psychiatric comorbid and/or unstable condition

As shown in Table 1, candidates will be provided with a detailed diagnostic confirmation using the Autism-Spectrum Quotient, Japanese version [23], which is a self-report questionnaire measuring the degree to which any adult with a normal IQ possesses traits related to the autistic spectrum. Additional measures will include the Social Responsiveness Scale for Adults, Japanese version [24], which measures the severity of autism spectrum symptoms (completed by a relative), and the Empathizing- Systemizing Quotient, Japanese version [25], which assesses a person’s strength of interest in empathy (defined as the drive to identify with a person’s thoughts and feelings and respond with an appropriate emotion). A person’s strength of interest in systems is defined as the drive to analyze or construct a system. Additionally, interviews using the ADOS for individuals with ASD and interviews with parents using the ADI-R will be conducted. Final participation will be decided after confirmation that the subject meets participation criteria.

ADI-R, Autism Diagnostic Interview, Revised; ADOS, Autism Diagnostic Schedule; ASD, autism spectrum disorders; AQ, Autism-Spectrum Quotient; CES-D, Center for Epidemiological Studies Depression Scale; CISS, Coping Inventory for Stressful Situations; DSM-IV-TR, text revision of the diagnostic and statistical manual of mental disorders, fourth edition; Dx, Diagnosis; E-SQ, Empathizing-Systemizing Quotient; GAF, Global Assessment of Functioning; LSAS, Liebowitz Social Anxiety Scale; M.I.N.I., Mini-International Neuropsychiatric Interview; MPMR, Motion Picture Mind-Reading task; SCQ, Social Communication Questionnaire; SPAI, Social Phobia and Anxiety Inventory; SRS-A, Social responsiveness scale for adults; STAI, State-trait Anxiety Inventory; TAS-20, 20-item Toronto Alexithymia Scale; WAIS-III, Wechsler Adult Intelligence Scale- Third Edition; WHO-QOL 26, World Health Organization Quality of Life 26-item version.

### Assessments/measures

#### Primary outcomes

Our hypothesis is that CBT will help adults with ASD to understand their own and others’ emotions and thoughts and to exercise emotion regulation, by increasing their knowledge of ASD and self-awareness, especially their own strength and weakness related to ASD. Therefore, primary outcome measures will be the 20-item Toronto Alexithymia Scale, Japanese version (TAS-20) [26] scores at post-intervention to evaluate the ability to understand one’s own mind and the percentage of correct response on the Motion Picture Mind-Reading task (MPMR) [27] at post-intervention to evaluate the ability of understanding the minds of others. As other primary outcome measures, we will also adopt the Coping Inventory for Stressful Situations, Japanese version (CISS) [28] scores at post-intervention to assess coping skills during stressful situations and the ASD questionnaire scores at post-intervention to assess the knowledge about ASD and the attitude for ASD. These measures are described in greater detail below.

The TAS-20 is one of the most commonly used measures of alexithymia. Alexithymia is characterized by a difficulty in identifying and describing emotions and the tendency to minimize emotional experience and focus attention externally. This measure is a self-report one and consists of 20 items and three factors: difficulty in identifying feeling, difficulty in describing feeling, externally oriented thinking. Each items is rated from 1 (strongly disagree) to 5 (strongly agree) and the total score ranges from 20 to 100. The time required for this test is about 5 minutes.

The MPMR, developed by Wakabayashi and Katsumata [27], involves advanced theory of mind tasks. Tasks are based on the scenes from a television drama. A total of 41 video clips (each 3 to 11 seconds in length) are included from the television drama series, *Shiroi Kyotō* [The White Tower], which depicts malpractice in a famous Japanese medical school. The participant is asked to judge whether the word or phrase presented on the screen aptly describes the person in each scene. The time required for this test is about 15 minutes.

The CISS determines the preferred coping style of an individual and assesses the relationship between the individual’s coping style and his or her personality. Its results are useful for treatment and intervention planning. The CISS measures three types of coping styles: task-oriented, emotion-oriented, and avoidance coping. This measure is also based on self-reports. The CISS consists of 48 items and each item is rated from 1 (not at all) to 5 (very much). The total score of each of the three coping styles ranges from 16 to 80. The time required for this test is about 10 minutes.

The ASD questionnaire that assesses the knowledge about ASD and the attitude to ASD was developed for this study. The questionnaire involved 10 knowledge-based questions (1 = true to 3 = not true) and five attitude-based questions (1 = disagree to 5 = agree) regarding ASD. The time required for this test is about 5 minutes.

#### Secondary outcomes

We anticipate that they will experience improvement in anxiety and depressive symptoms and their adaptation to their lives as a result of their improved awareness of their own and others’ mind, increased knowledge about ASD, and enhanced coping skills for emotion-regulation. Thus, secondary outcome measures will be the scores of the TAS-20, the CISS and the ASD questionnaire and the percentage of correct response on the MPMR at 12 weeks follow-up and the scores of the State-trait Anxiety Inventory (STAI) [29], the LSAS [30], the SPAI [31], the Center for Epidemiological Studies Depression Scale (CES-D) [32], the Global Assessment of Functioning, Japanese version (GAF) [18] and the World Health Organization Quality of Life 26-item version, Japanese version (WHO-QOL 26) [33] at post-intervention and 12 weeks follow-up. These measures are described in greater detail below.

The STAI is a self-report questionnaire that includes separate measures for state and trait of anxiety. The STAI consists of 20 items each for state and trait of anxiety. Each item for state anxiety is rated from 1 (not at all) to 4 (very much so) and each item for trait anxiety is rated from 1 (almost never) to 4 (almost always). The total score for each ranges from 20 to 80 The time required for this test is about 10 minutes.

The SPAI is a self-report questionnaire that assesses specific somatic symptoms, cognitions, and behaviors across a wide range of potentially fear-inducing situations to measure social anxiety and fear. The SPAI consists of 109 items and two domains: social phobia and agoraphobia. Each item is rated from 0 (never) to 6 (always). The social phobia score ranges from 0 to 192 and the agoraphobia score ranges from 0 to 78. The time required for this test is about 25 minutes.

The LSAS is a questionnaire designed to assess the range of social interactions and performance situations that individuals with social phobia may fear and/or avoid. This measure was designed as a self-report questionnaire, but we use it here in the form of an interview. The LSAS comprises 24 social situations that are each rated for level of fear (0 = none to 3 = severe) and avoidance (0 = none to 3 = usually). The total score ranges from 0 to 144. The time required for the interview is about 10 minutes.

The CES-D is a self-report screening tool for depression and consists of 20 items. Each item is rated from 1 (absent) to 4 (five or more times a week), and the total score ranges from 0 to 60. The time required for this test is about 5 minutes.

The GAF is used by clinicians to make a global assessment of an individual’s adaptive level of functioning on a scale from 0 (poor) to 100 (good). The time required for this interview is about 30 minutes.

The WHO-QOL 26 is used to measure an individual’s subjective sense of wellbeing and quality of life, rather than determining the possible presence of an illness. The WHO-QOL 26 consists of 26 items and four domains: physical health, psychological health, social relationships, and environment. Each item is rated from 1 (poor) to 5 (good) and presented as an average score. The time required for this test is about 5 minutes.

It takes about 1 hour for the participant to fill out all of the questionnaires; therefore, they will be sent via mail to their home 7 to 10 days before the assessment date with careful consideration of the participants’ burden. During the pre-, post-, and follow-up assessments, the GAF and LSAS interviews will take about 30 minutes. The theory of mind tasks, MPMR (done on a PC) will take about 15 minutes.

### Details of the intervention program

The CBT group will receive group therapy over an 8 week period (1 session/week) with each session lasting approximately 100 minutes. Each session will include a short period of relaxation between topics (Table 2). Group therapy consists of four to five adults with ASD and two therapists. The therapist who conducts the group therapy as the leader is the certified developmental psychologist who has a PhD and over 10 years experience working with individuals with ASD. The other therapist, the sub-leader, is also a psychologist and has a Masters degree. One or two typical-development volunteers will also join the group and do the same program as the participants with ASD.

**Table 2 T2:** Timetable of one session

**Schedule**		
5 minutes	Greeting	
30 minutes	Psychoeducation on autism spectrum disorders	
10 minutes	Relaxation	
40 minutes	Work and discussion	
	<Topics>	
	Session 1 Autism spectrum disorders	Session 2 Relaxation
	Session 3 Happiness	Session 4 Comfort
	Session 5 Affection	Session 6 Anxiety
	Session 7 Anger	Session 8 Coping skills
5 minutes	Relaxation	

The program has two parts; one is the psychoeducation on ASD and the other is the emotion-regulation program. Materials for the psychoeducation on ASD prepared for this study will be used for learning and understanding the nature of ASD. The Cat-kit [16] will be used for the emotion-regulation program. The titles of each session are as follows: (1) the characteristics of autism; (2) relaxation 1 and happiness; (3) relaxation 2 and comfort; (4) differences from others and sadness; (5) strengths and anxiety; (6) weaknesses and coping with anxiety; (7) anger and coping methods; (8) summary: autism characteristics and conveying emotions.

During each session, participants will be asked to do some written work. For the part of psychoeducation on ASD, they will describe and present their own preferences, strengths, weaknesses, *et cetera*. In the emotion-regulation program, they will present their experience and physiological changes associated with emotion. The typical-development volunteers will also perform the same tasks. Finally, after completion of the intervention, the individuals with ASD will make out an original notebook containing descriptions of the nature of ASD and emotion-regulation learning and they will be encouraged to use this for continued study.

### Randomization

Enrollment and random allocation will be performed through central registration at the University Hospital Clinical Trial Alliance Clinical Research Supporting System (UHCT ACReSS) at the University of Tokyo. A minimization method will be used with sex as the allocation factor. A third party, who is not involved in this trial, will enroll participants after examining their eligibility and informed consent. Owing to allocation concealment, the random allocation sequence will be provided by UHCT ACReSS and will not be revealed to any researchers or staff until the end of the enrollment period. As this is a single-blinded trial, all assessments will be conducted by raters without knowledge of whether the participant is in the CBT or waitlist conditions.

### Statistical methods

All analyses will be performed using SPSS 20 J (SPSS Inc., Chicago, IL, USA). All data will be analyzed under the intent-to-treat principle. For the primary outcomes, independent *t*-tests will be used to compare changes in scores between the pre-assessment and post-assessment periods between the CBT group and the waitlist control group. The primary outcomes will be analyzed controlling for potential confounds (for example, age, gender, IQ, and clinical characteristics) using regression models. Secondary outcomes will be analyzed using relevant tests at each assessment, controlling for possible confounds as described above. Subgroup analyses will be performed for any possible confounds to differentiate the efficacy of CBT at follow-up.

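### The primary outcomes are defined as post-intervention scores but tested as change by an unadjusted t-test, beside an unranked regression with open covariates; one pre-specified baseline-adjusted ANCOVA would be more precise and settle which model decides

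*Protocol article*

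**What the plan says.** The Primary outcomes section sets each endpoint at one time point. It opens: "Therefore, primary outcome measures will be the 20-item Toronto Alexithymia Scale, Japanese version (TAS-20) [26] scores at post-intervention". The mind-reading task is likewise taken "at post-intervention to evaluate the ability of understanding the minds of others", the coping inventory as "scores at post-intervention to assess coping skills during stressful situations", and the last measure as "the ASD questionnaire scores at post-intervention to assess the knowledge about ASD and the attitude for ASD".

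The Statistical methods section gives two analyses of these outcomes. First, independent t-tests "will be used to compare changes in scores between the pre-assessment and post-assessment periods between the CBT group and the waitlist control group". Then: "The primary outcomes will be analyzed controlling for potential confounds (for example, age, gender, IQ, and clinical characteristics) using regression models". The article does not say which of the two is decisive, what the dependent variable of the regression is, or whether the measure's own pre-intervention score is a covariate.

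Under Randomization: "A minimization method will be used with sex as the allocation factor". Sex is therefore the one design factor. It is absent from the t-test and appears in the regression only as an example. Table 1 shows that all four primary measures are taken before the intervention as well as after it.

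**The concern.** Three features of the text do not fit together well.

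- The endpoint is a score at one time, but the test is on change.
- The test on change uses the baseline inefficiently. Subtracting the whole baseline value is optimal only if the post score moves one-for-one with it. At any lower correlation the subtraction adds noise, which matters in a trial planned for 25 analysed participants per arm.
- Two analyses of the same outcomes stand side by side, and the covariates of the second are open. Unless one is named as decisive before the data are seen, the more favourable result can be chosen.

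At stake are some power, possibly a good deal, and a modest excess of false positive findings on each primary measure.

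**Working it through.** **Inputs from the article.** 25 participants per group wanted and 30 recruited (Participants); 1:1 allocation (Trial design). The article shows no power calculation, so there is no power figure to reproduce. The recruitment arithmetic is consistent: 25/30 implies 16.7% dropout, and 2 × 30 = 60.

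**Assumptions, because the article does not give them.** Two-sided alpha 0.05; equal SD (set to 1) before and after; a true difference of 0.6 SD of the post score; pre-post correlation r from 0.3 to 0.9.

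**Variance per participant.**
- Change score: 1 + 1 − 2r = 2(1 − r).
- ANCOVA on baseline: 1 − r².
- Ratio, ANCOVA to change: (1 − r)(1 + r) / [2(1 − r)] = (1 + r)/2.

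Estimating the ANCOVA slope multiplies its variance by about 1 + 1/46 = 1.022 with 25 per arm. This is charged in the power figures below.

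**Power.** The noncentrality is 0.6 / √(2V/25), where V is the variance per participant. The t distribution has 48 degrees of freedom for change and 47 for ANCOVA. At r = 0.5, change gives 0.6 / √(2 × 1.00/25) = 2.12, and ANCOVA gives 0.6 / √(2 × 0.75 × 1.022/25) = 2.42.

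| r | V, change | V, ANCOVA | Ratio | Power, change | Power, ANCOVA |
|---|---|---|---|---|---|
| 0.3 | 1.40 | 0.91 | 0.65 | 42% | 58% |
| 0.5 | 1.00 | 0.75 | 0.75 | 55% | 66% |
| 0.7 | 0.60 | 0.51 | 0.85 | 77% | 82% |
| 0.8 | 0.40 | 0.36 | 0.90 | 91% | 93% |
| 0.9 | 0.20 | 0.19 | 0.95 | 99.6% | 99.7% |

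**Does the change score estimate something else?** Let δ be the true effect and d the chance difference between arms at baseline. Given d, the expected difference in post scores is δ + rd, so the expected difference in change is δ + (r − 1)d. Randomisation makes d average zero, so both have expectation δ. In a single trial the shift need not be zero. The standard error of d with 25 per arm is √(2/25) = 0.28 SD, so at r = 0.5 a one-standard-error imbalance moves the change estimate by 0.5 × 0.28 = 0.14 SD. ANCOVA removes this conditional shift.

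**Type I error if the more favourable analysis is taken.** Data were simulated under no effect, and success was counted if either analysis was significant at 5%.
- Change t-test, or a regression of change on arm and three covariates unrelated to outcome (standing in for age, sex and IQ): about 6%.
- Change t-test, or a regression that includes baseline: 7.6% at r = 0.5 and 6.6% at r = 0.7 with 25 per arm; about 7% at r = 0.6 with 30 per arm.

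**The case against.** The strongest reply is that the planned test is sound. Under 1:1 randomisation the difference in mean change and the difference in mean post score have the same expectation. That stands. A reader might infer from the mismatch of endpoint and test that the t-test is biased or addresses a different effect. The documents do not support this: the mismatch is one of definition and efficiency, and the only bias is conditional on a chance baseline imbalance.

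Second, the gain depends on an unknown correlation. The Background describes alexithymia as a personality construct, so a high r is plausible for at least the TAS-20, and at 0.8 or above little is gained. This also stands, and it is why the table runs to 0.9.

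Third, the ordinary reading may be a main t-test with a supportive adjusted analysis, and a full protocol or SAP, not shown, may fix the ranking, the covariates and the dependent variable. Clinical characteristics could even include baseline scores. This is fair as far as detail goes, and it limits how serious the point is. It does not remove what the article itself states: endpoints defined one way and tested another, and two analyses of the primary outcomes with no order between them.

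Fourth, a reader might take 7% as the plan's type I error. It is not. It requires both a choice made after seeing results and a regression that includes baseline, which the listed examples do not name. With three unrelated covariates the figure is about 6%. An open search over covariates could cost more, but that was not computed. Nor does leaving sex out of the t-test inflate its type I error.

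**Conclusion.** The point holds as a matter of efficiency and pre-specification and should be fixed; it does not invalidate the trial. With 25 per arm and an assumed 0.6 SD effect, ANCOVA adds about 16, 11, 5 and 2 percentage points of power at r = 0.3, 0.5, 0.7 and 0.8, and nothing material at 0.9. These figures rest on equal SDs, approximately normal data and two-sided 0.05, none of which the article states. The unranked pair of analyses would cost one to two percentage points of type I error per outcome if the better result were chosen.

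A reader might also infer that one ANCOVA would resolve all choice in the primary analysis. It settles the model for each score only. Four primary measures remain, the coping inventory alone yielding three scores, and that multiplicity needs its own rule.

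**What to change.** Make the single primary analysis of each primary score an ANCOVA of the post-intervention score on arm, that measure's own pre-intervention score and sex, and report the adjusted mean difference with its 95% confidence interval. This keeps the endpoint as the Primary outcomes section defines it and includes the minimization factor. Label the change-score t-test and the regression with wider covariates as sensitivity analyses, and list the covariates of the latter.

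The cost is a documented change, not new data. Every baseline score needed is already scheduled in Table 1, and no extra participants or visits are required. The Trial status section reports 88% of participants included and 68% of those already tested at follow-up, so the change needs a dated amendment made before any outcome is examined by arm.

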## Methods/Design

### Trial design

This study is a randomized controlled trial. It follows a waitlist control, single-blinded (participants and psychologists who conduct the group-based CBT are not blinded and the assessors of all measures are blinded) design. The allocation of participants will be equal (1:1) across a CBT group (intervention group) and a waitlist control group. All assessment will be administrated by the blinded assessors at the enrolment, post-intervention, and at 12 weeks follow-up. The entire trial design is illustrated in Figure 1. First, an assessment for eligibility will be performed. For individuals who meet the inclusion criteria, a pre-assessment will be performed no more than 4 weeks before the treatment. After pre-assessment, participants will be allocated into the immediate treatment condition or the waitlist condition. After the completion of treatment, post-assessment will be performed within 4 weeks. After an additional 12 weeks, a follow-up assessment will be performed. The pre-assessment and intervention will be conducted at the Department of Child and Adolescent Mental Health, the National Institute of Mental Health, National Center of Neurology and Psychiatry, and the Department of Child Psychiatry, the University of Tokyo Hospital. The allocation and post- and follow-up assessments will be conducted at the Department of Child Psychiatry, the University of Tokyo Hospital.

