**Figure 1 F1:**
[figure not shown]
**CONSORT flow chart of the clinical trial.** The allocation of participants will be equal (1:1) across a cognitive-behavioral therapy group and a waitlist control group. All assessment will be administrated at the enrolment, post-intervention, and at 12 weeks follow-up. Both pre- and post-assessment will be performed at 4 weeks before or after the treatment.

The target sample size is 60, and registration began on September 1, 2011. This trial was registered in the University Hospital Medical Information Network Clinical Trials Registry and approved by the International Committee of Medical Journal Editors (No. UMIN000006236).

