### Participants

The participants will be individuals diagnosed with pervasive developmental disorder based on the text revision of the diagnostic and statistical manual of mental disorders, fourth edition (DSM-IV-TR) criteria [18]. In our study, the Cat-kit [16], which was used in the studies of Sofronoff and colleagues, will be used, along with the procedure of those studies. Sofronoff and colleagues had 23 to 25 participants in each of their intervention groups. Therefore we decided to use 25 participants each for the intervention and control groups, recruiting 30 individuals per group to account for potential dropouts.

The inclusion criteria are as follows: (1) age between 18 and 50 years; (2) a full intelligence quotient (IQ) of at least 85 and a verbal IQ of 100 or above (IQ will be evaluated using the Wechsler Adult Intelligence Scale, Third Edition [19]); (3) a specific diagnosis based on the Autism Diagnostic Schedule (ADOS) [20] or the Autism Diagnostic Interview, Revised (ADI-R) [21] with a score above the ASD cut-off; (4) high school graduate or above; (5) knowledge of one’s diagnosis, (6) realization of one’s poor emotional self-awareness/ability to express emotion and poor understanding of others’ emotions and thoughts, and (7) willingness to participate. Individuals with a comorbid psychiatric and/or unstable condition will be excluded (Table 1). The Mini-International Neuropsychiatric Interview [22] will be used to evaluate psychiatric co-morbidity. Any individual who fails to attend more than three sessions will be regarded as 'dropping out', but supplementary instruction will be regarded as equivalent to attendance and will be offered up to three times. Current medication doses should not be increased greatly during the trial. Furthermore, current individual psychological therapy and regular medical treatment will be continued during the intervention. A detailed ASD assessment and diagnosis will be carried out for all intervention candidates. Recruitment of individuals with an ASD diagnosis will be conducted through the Department of Child Psychiatry or Neuropsychiatry at the University of Tokyo Hospital or an advertisement on the University of Tokyo Hospital web site.

**Table 1 T1:** All measures assessed at enrollment, pre-intervention, post-intervention, and follow-up, including primary and secondary outcomes

**Measures**	**Time required (minutes)**	**Dx data**	**Pre-intervention**	**Post-intervention**	**Follow-up**

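### CBT is given in therapy groups of four to five, but the primary t-test treats every participant as independent; if outcomes correlate within groups, its standard error is too small

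*Protocol article*

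**What the plan says.** Participants are allocated individually: "The allocation of participants will be equal (1:1) across a CBT group (intervention group) and a waitlist control group" (Protocol article, Trial design). The treatment is then given in groups: "Group therapy consists of four to five adults with ASD and two therapists" (Details of the intervention program). Contact is substantial: "The CBT group will receive group therapy over an 8 week period (1 session/week) with each session lasting approximately 100 minutes". The timetable in Table 2 sets aside 40 minutes of each session for work and discussion, and members share personal material: "In the emotion-regulation program, they will present their experience and physiological changes associated with emotion". The document describes no group contact for waitlist participants before the post-assessment.

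For the primary outcomes, the Statistical methods section states that independent t-tests "will be used to compare changes in scores between the pre-assessment and post-assessment periods between the CBT group and the waitlist control group". It adds: "The primary outcomes will be analyzed controlling for potential confounds (for example, age, gender, IQ, and clinical characteristics) using regression models". Therapy group, clustering, an ICC or a design effect appears neither there nor in the sample-size text, which reads: "Therefore we decided to use 25 participants each for the intervention and control groups, recruiting 30 individuals per group to account for potential dropouts".

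**The concern.** Individual randomisation makes participants independent at entry. It does not keep them so once one arm is treated in small groups that talk, work and present to each other for eight weeks. The result is a partially nested design: outcomes may be correlated within therapy groups in the CBT arm, while each waitlist participant stands alone. An independent t-test takes its standard error from the spread of individuals and credits the CBT arm with 30 independent observations. With positive within-group correlation the arm carries less information than that. P-values are then too small and confidence intervals too narrow for all four primary measures.

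The regression as described does not repair this, because age, gender, IQ and clinical characteristics all describe the participant and not the group. Nor is this a detail that a condensed article leaves to a fuller plan: the article itself names the test.

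**Working it through.** **The plan's own figures.** 30 + 30 = 60, which matches the stated target. An allowance of 5 in 30 (16.7%) takes 30 recruited to 25 analysed per arm. No alpha, power, effect size or standard deviation is given, so the sample size cannot be reproduced from a power calculation. None is needed here.

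**Inputs.**
- Per arm: 30 recruited, or 25 analysed (Participants).
- Therapy-group size: 4 to 5 (Details of the intervention program).
- ICC: not stated; 0 to 0.30 assumed.
- Alpha: not stated; two-sided 5% assumed.

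**How many groups.** Six groups of 5 make 30. Five groups of 4 plus two of 5 make 30. Eight groups of at least 4 would need 32. So only 6 or 7 groups fit.

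**Formulas**, with equal total variance in the two arms:
- effective group size m = sum of squared group sizes / 30. Six groups of 5: m = 5. Seven groups: m = (5 × 16 + 2 × 25)/30 = 4.33.
- design effect in the CBT arm: DE = 1 + (m − 1) × ICC.
- true SE / t-test SE = √((DE + 1)/2), since only one arm is inflated.
- actual alpha = 2 × (1 − Φ(1.96 / ratio)).

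**Worked example, ICC 0.10.**
- Six groups of 5: DE = 1 + 4 × 0.10 = 1.40; ratio = √1.20 = 1.095; 1.96/1.095 = 1.790; alpha = 7.4%.
- Seven groups: DE = 1 + 3.33 × 0.10 = 1.333; ratio = √1.167 = 1.080; 1.96/1.080 = 1.815; alpha = 7.0%.

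**Results for 30 per arm.** The last column is from 100,000 simulated null trials per setting.

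| ICC | SE ratio, 7 / 6 groups | Alpha by formula, 7 / 6 groups | Alpha by simulation, 7 / 6 groups |
|---|---|---|---|
| 0 | 1.00 / 1.00 | 5.0% / 5.0% | 5.1% / 5.1% |
| 0.05 | 1.04 / 1.05 | 6.0% / 6.2% | 6.0% / 6.1% |
| 0.10 | 1.08 / 1.10 | 7.0% / 7.4% | 7.0% / 7.4% |
| 0.20 | 1.15 / 1.18 | 9.0% / 9.8% | 9.1% / 9.7% |
| 0.30 | 1.22 / 1.26 | 11.0% / 12.1% | 11.2% / 12.3% |

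At the midpoint size of 4.5 the ratios are √((2 + 3.5 × ICC)/2) = 1.04, 1.08, 1.16 and 1.23 for ICC 0.05, 0.10, 0.20 and 0.30. With 25 per arm the simulated alphas differ little: 6.0-6.2%, 6.8-7.3%, 9.1-9.9% and 11.0-12.4%.

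**Direction.** Simulated false positives split evenly. With six groups of 5 and ICC 0.10, about 3.7% wrongly favour CBT and about 3.7% wrongly favour waitlist, against 2.5% each for a valid test.

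**Does allowing for group restore the level?** A Satterthwaite test of CBT group means against individual waitlist values was simulated over ICC 0 to 0.30. It gave 5.0-5.3% with six groups of 5 against 30 controls, and 5.1-5.4% with five groups of 5 against 25.

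**The case against.** The strongest reply is that the inflation is conditional and may be small. The document gives no ICC, and at ICC 0 the planned test holds its level. Some features argue for a low ICC: the timetable and session titles are fixed, a kit supplies the emotion-regulation material, and the mind-reading task is done on a PC. The leader and sub-leader are described in the singular. If the same two people run every group, therapist effects are common to the whole CBT arm and add nothing to the correlation within groups. At ICC 0.05 to 0.10 the excess is only about 1 to 2.5 percentage points, and nothing in the document points to 0.20 or 0.30. All of this stands, and it limits the severity. It does not show that the ICC is zero: discussion and group composition are still shared, and exchange between members is part of the programme.

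Stronger readings are tempting but not supported:
- **That the error always favours CBT.** Ignoring the grouping shrinks the standard error but does not bias the estimate, so both directions are inflated alike.
- **That false positives certainly exceed 5%.** This needs a positive ICC, and the 5% level is itself an assumption.
- **That every secondary outcome is affected.** The protocol assigns these only unspecified relevant tests, so the fault is fixed in the text for the primary t-test alone.
- **That the groups are closed.** The document does not say so.

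A last objection concerns the remedy. With six groups of 5, the group variance in a mixed model is estimated as zero in roughly 43-44% of trials at ICC 0.05 and 33% at 0.10. An approximation to that model's type I error gives about 3.8% at ICC 0, 4.1-4.2% at 0.05 and 4.5% at 0.10. It is thus somewhat conservative at low ICC. That is a real cost and should be stated.

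**Conclusion.** The point holds in conditional form. The plan names a primary test that assumes independence while one arm is treated in 6 or 7 groups, and the adjusted regression as described does not correct for this. If the ICC is positive, the size is modest at 0.05-0.10 (true alpha about 6-7%) and considerable at 0.20-0.30 (about 9-12.5%). These figures rest on an assumed two-sided 5% level, an assumed ICC range and equal total variance in the arms. They apply to each primary measure separately and leave aside multiplicity across the four. Severity: should be fixed. The unknown ICC argues against ranking it higher; a cheap remedy that holds its level argues against leaving it.

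**What to change.** Record each participant's therapy-group identifier in the dataset. Replace the independent t-test as the primary analysis with one that allows for therapy group in the CBT arm only. Either of these would serve:
- a partially nested mixed model, with a random group intercept in the CBT arm, each waitlist participant as a cluster of one, arm-specific residual variance, and Satterthwaite or Kenward-Roger degrees of freedom; or
- a Satterthwaite test of CBT group means against individual waitlist values.

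Choose one before the data are analysed, keep the group term whatever its p-value, and report the ICC for each primary outcome.

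The change needs only analysis wording and one variable. Recruitment, treatment and assessment stay as they are, so it remains feasible with 88% of participants already included (Trial status). The price is wider intervals, fewer degrees of freedom and some loss of power with only 6 or 7 groups. The mixed model may also be somewhat conservative when the ICC is near zero; the group-means test was close to 5% throughout the range examined.
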